### Project measures (Table 3)

#### Tobacco abstinence

Outcome measures are adapted from the Society for Research on Nicotine and Tobacco’s Workgroup on Abstinence Measures and Workgroup on Biochemical Verification [29, 30]. Our primary endpoint is 7-day, verified cigarette abstinence at 1 month after enrollment. Subjects with missing data will be counted as smokers.

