#### Verification of abstinence

We will use either mailed salivary cotinine or in-person carbon monoxide (CO) testing to confirm smoking status. Participants who report 7-day point-prevalence abstinence, and who are not taking NRT, will be asked to provide a saliva sample. Cotinine is the measure of choice because of its sensitivity and specificity [30]. Samples will be stored in a − 20 °C freezer until laboratory analysis. Participants who are still using NRT, or who refuse salivary cotinine, will be verified via CO testing. Those with < 10 ppm will be considered abstinent.

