#### Intervention costs

We will prospectively track variable intervention costs. Costs will include inpatient counselor services, post-discharge counseling time, and initial pharmacotherapy dispensed at baseline. During the 6-month follow-up call, we will ask participants to recall their use of pharmacotherapy after the initial supply. Personnel time will be valued at Bureau of Labor Statistics (www.bls.gov) wages plus benefits for an appropriately trained health-promotion professional. Pharmacotherapy costs will be based upon retail prices estimated from on-line pharmacy websites. Intervention costs will be tracked as they are incurred. We will exclude research costs. We will not discount either costs or benefits.

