#### Protection against risks

There are minimal risks in this study. Any emails used to transmit study participant information will be encrypted to protect the privacy of patients. Salivary cotinine samples are noninvasive; samples will be labeled with participants’ study ID numbers, rather than names, to protect participants’ privacy. When collecting proxy verification of smoking status, no information about the patients’ participation in the trial will be provided to the proxy besides the participants’ name and the fact that they had nominated the proxy to provide verification of smoking status at the end of a health-promotion study.

Standard language in our consent procedure assures the participants of the confidential nature of the study. Those who elect to participate will be clearly told that they may withdraw from the study at any time without jeopardizing current or future care at any medical facility. Potential participants will also be informed of alternative treatments (i.e., using other smoking-cessation programs, purchasing nicotine gum, patches, or lozenges from the pharmacy, obtaining a prescription for a nicotine inhaler, nasal spray, or other smoking-cessation products from their physician). These standards are strictly adhered to and monitored by the KUMC Institutional Review Board. Only summaries of group data will be reported in any publications or presentations, with no identification of individuals. All records will be kept in locked filing cabinets in offices that are kept locked when unoccupied. Subject files will be kept in a secure area, with access only by designated staff members (PI and co-investigators).

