Hypothesis 1: compared to OPT IN, significantly more patients in OPT OUT will participate in counseling, use cessation medications, and be abstinent from smoking	Abstinence: treatment condition and 1-month 7-day point-prevalence abstinence	2-sample binomial test
	Counseling: treatment condition and total counseling time by 1 month	2-sample lognormal test
	Medication: treatment condition and number of days of medication use	2-sample Poisson test
Hypothesis 2: significantly more smokers in OPT OUT will be abstinent from smoking, and mediation analyses will partially or fully explain the effects	Treatment condition and 6-month and • 7-day point-prevalence abstinence • Default variables • Counseling/medication use	Bayesian structural equation modeling with a logistic outcome
Hypothesis 3: OPT OUT will be more costly but also more effective than OPT IN	Treatment condition and 1-month abstinence • Variable costs	Incremental cost/quit

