Aim 2. Hypothesis 3: OPT OUT will be more costly—in terms of upfront costs—but will be more effective than OPT IN. As a result, OPT OUT will be more cost-effective from a provider perspective. We will conduct a cost-effectiveness analysis to explicitly document the relative costs and benefits of OPT OUT versus OPT IN. Our cost analytic framework generally follows the guidelines adopted by the Centers for Disease Control (CDC) in accordance with the Consensus Panel on Cost-effectiveness in Health and Medicine [52–54]. We will divide the analysis into two components: first, intervention-only costs, and second, intervention plus short-term (6 months or less) costs post discharge. The primary cost-effectiveness analysis will be set up as an incremental cost-effectiveness ratio (ICER). Incremental cost-effectiveness analysis identifies the marginal benefit of switching from one intervention to the other and is the ratio of the difference in costs divided by the difference in effectiveness between the two study arms. The outcome assessed will be biochemically or proxy-verified 7-day point-prevalence abstinence. The ICER will indicate the added cost per additional quitter OPT OUT versus OPT IN, a metric that will allow comparisons to other smoking-cessation economic studies. While the societal perspective is recommended by current national guidelines, it requires quality-adjusted life years (QALYs) as the denominator [52]. Since this is a short-term study, we decided against attempting to estimate changes in QALYs, and focus instead on cost per quit and incorporate costs from a health care system perspective (direct costs only), comparable to a-priori cost analyses of several clinical trials based in Kansas [55, 56]. In sensitivity analyses, we will adjust wage rates upwards to the national average. In order be able to generalize our findings from this one clinical trial to other populations, we will explore how the variation in counseling time and effectiveness influence the relative cost-effectiveness of the treatment strategies. Our analyses will vary time and effectiveness until breakeven points are achieved between the treatment options.

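### Read together, the cost-effectiveness passages set costs to 6 months against 1-month quits and admit proxy-verified quits that the verification rule does not; horizon and quit definition should be reconciled.

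*Protocol article*

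**What the plan says.** All places are in the protocol article.

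**Costs.** Analyses by aim (Aim 2, Hypothesis 3) splits the cost analysis into two components: "first, intervention-only costs, and second, intervention plus short-term (6 months or less) costs post discharge". Intervention costs adds: "During the 6-month follow-up call, we will ask participants to recall their use of pharmacotherapy after the initial supply". Table 3 collects cost measures at months 1 and 6.

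**Effect: time point.** The Hypothesis 3 text gives no time point for the quit outcome. The Hypothesis 3 row of Table 5 does: "Treatment condition and 1-month abstinence", listed with variable costs and analyzed as incremental cost per quit. Table 3 shows that 7-day abstinence and its biochemical verification are collected at both month 1 and month 6.

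**Effect: who counts as a quitter.** For the ratio: "The outcome assessed will be biochemically or proxy-verified 7-day point-prevalence abstinence". For the trial, under Tobacco abstinence: "Our primary endpoint is 7-day, verified cigarette abstinence at 1 month after enrollment". Verification of abstinence then says: "We will use either mailed salivary cotinine or in-person carbon monoxide (CO) testing to confirm smoking status". CO is the fallback for participants still on NRT or refusing cotinine, and Table 3 lists only biochemical verification. Proxies appear in one other place, the confidentiality text of Protection against risks, which begins "When collecting proxy verification of smoking status" and ties them to no endpoint.

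**The concern.** A cost per additional quitter is interpretable when costs and quits cover the same period and a quitter is defined as in the trial's effect estimate. Two features of the text put this in doubt.

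First, costs incurred after the 1-month assessment cannot have produced a 1-month quit. If such costs are divided by the 1-month difference, the result is neither a 1-month nor a 6-month cost per quit.

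Second, a participant who reports abstinence, gives no sample and has a confirming proxy fails the verification rule but counts as a quitter in the ratio. The denominator can then differ from the reported abstinence difference.

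The ratio is the result for Hypothesis 3, and the article intends it for comparison with other economic studies of smoking cessation. With two quit definitions and two collection times in the text, the choice between them could be made after the results are known.

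**Working it through.** **1. Passages side by side**

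| Element | Analyses by aim | Table 5 (Hypothesis 3) | Elsewhere |
|---|---|---|---|
| Cost horizon | Intervention only; then up to 6 months after discharge | Variable costs, no horizon | Later drug use recalled at 6 months (Intervention costs) |
| Quit time point | None given | 1 month | Measured at months 1 and 6 (Table 3) |
| Verification | Biochemical or proxy | Not stated | Cotinine or CO (Verification of abstinence); biochemical (Table 3); proxy collection described (Protection against risks) |

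The only time point given for the Hypothesis 3 effect is 1 month, and the longest cost window is 6 months. Post-discharge counseling is confined to the 4 weeks after discharge. Of the tracked intervention costs, it is therefore mainly medication used after the starter pack that can fall beyond month 1. Because the 6-month recall sits under Intervention costs, these later costs may enter the first component as well as the second.

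**2. Planned difference reproduced** (inputs from Projected quit rates)

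- OPT IN: 0.30 × 0.29 + 0.70 × 0.10 = 0.157
- OPT OUT: 0.80 × 0.29 + 0.20 × 0.10 = 0.252
- Difference: 0.252 − 0.157 = 0.095, or 1/0.095 = 10.5 patients per additional quitter

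Both rates match the article. It gives no cost figures, so no ratio can be computed, only its scaling.

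**3. Scaling**

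The ratio is ΔC/d, with ΔC the cost difference and d the quit-rate difference. For fixed ΔC, moving from 9.5 points to another difference d′ multiplies the ratio by 9.5/d′.

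**4. Horizon** (share of the 1-month difference present at 6 months is assumed)

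| Share at 6 months | 6-month difference (points) | 6-month-matched ratio relative to one on 1-month quits |
|---|---|---|
| 125% (widening) | 11.875 | 9.5/11.875 = 0.80 |
| 100% | 9.5 | 1.00 |
| 75% | 7.125 | 9.5/7.125 = 1.33 |
| 50% | 4.75 | 9.5/4.75 = 2.00 |

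**5. Proxy quits** (points added to each arm are assumed)

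| Added to OPT IN | Added to OPT OUT | Difference (points) | Ratio relative to biochemical only |
|---|---|---|---|
| 0 | 0 | 9.5 | 1.00 |
| 2 | 2 | 9.5 | 1.00 |
| 0 | 2 | 11.5 | 9.5/11.5 = 0.83 |
| 2 | 0 | 7.5 | 9.5/7.5 = 1.27 |
| 0 | 5 | 14.5 | 9.5/14.5 = 0.66 |
| 5 | 0 | 4.5 | 9.5/4.5 = 2.11 |

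Equal additions cancel; unequal ones move the ratio either way. There is some reason to expect inequality. Planned service uptake is 80% against 30%, and participants still on NRT need in-person CO rather than a mailed sample, so missing samples could differ by arm. That is inference; the article gives no proxy rate.

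**The case against.** The strongest reply is that the mismatch is inferred. No sentence divides 6-month costs by 1-month quits. The Hypothesis 3 text gives no time point for the quit outcome, the 6-month limit is an upper bound, and the one-line Table 5 row, with its variable costs, can be read as describing the intervention-only component alone. Six-month verified abstinence is collected, so a matched ratio is open to the analysts, and a condensed article may leave the pairing to a fuller plan. All of this stands as a limit on the claim. It does not remove the point: Table 5 names only 1 month for this hypothesis, and taking the text as written gives unmatched horizons.

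On verification, the inconsistency runs across the document and is not located in the cost section alone. Protection against risks treats proxy verification as a planned procedure, so the verification section may simply have left it out. That also stands. The passages need reconciling, and the cost section cannot be presumed to be the one in error.

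A reader might also infer more than the text supports:

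- *That cost per quit is understated by a definite factor.* The article gives no 6-month difference. No narrowing gives a factor of 1.0, and widening would reverse the direction.
- *That a 1-month denominator departs from the trial's own effect.* One month is the primary time point; only the proxy wording can separate the ratio's 1-month effect from the reported one.

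The planned breakeven analysis varies effectiveness and would show how the ratio responds to a smaller difference. It does not settle which observed difference enters the main ratio.

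**Conclusion.** The point holds in limited form. Taken together, Analyses by aim and Table 5 leave the second ratio with costs to 6 months over 1-month quits, and the ratio's quit definition is wider than the verification rule and Table 3 allow. These are conflicts between stated rules, not only omitted detail.

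Size and direction cannot be determined from the article. The multipliers in the working rest on assumed 6-month differences and assumed proxy additions, and each takes the cost difference as fixed. They show sensitivity and estimate no bias.

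The primary abstinence analysis, the adaptive allocation and the stopping rule are untouched. The correction is worth making because the ratio is a hypothesis-level result and the 6-month verified outcome needed for matching is already collected.

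**What to change.** In the Hypothesis 3 text and the Table 5 row:

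1. Pair intervention costs with 1-month verified quits, and costs to 6 months with 6-month verified quits. State whether medication use recalled at 6 months belongs to the first component or only to the second.
2. Use the same verification definition for the ratio as for the abstinence endpoint. Reconcile Verification of abstinence, Protection against risks and Analyses by aim so that all three agree on the role of proxies. Keep any proxy-verified version as a labeled sensitivity analysis.
3. State an assumption for missing costs in the 6-month ratio. Missing quits are counted as smoking, but the article gives no counterpart for costs. Later medication use comes from recall at the 6-month call, and the article expects to have no data on patients who refuse consent at 1 month.

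No new data collection is needed. Items 1 and 2 are short text changes, which for item 2 extend beyond the cost section; item 3 requires an analytic decision. The price is a 6-month ratio that may be less favorable and less precise and that depends on the missing-cost assumption.

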## Discussion

### Research contribution

Missed opportunities for providing medications and counseling for tobacco dependence has created a large treatment gap. This study innovatively reframes the rationale for this gap: what if low rates of treatment are caused *not* by smokers’ lack of motivation to quit, but by requiring patients to opt in to care? Viewed from this perspective, the effects of screening for readiness on tobacco-cessation treatment can be tested by changing the way that treatment is offered. This study also identifies a major rate-limiting step in access to tobacco-cessation treatment. Regardless of what population, setting, or approach is used to disseminate tobacco-cessation treatment, as long as providers screen for readiness, the majority of smokers will report that they are *not* ready to quit—and that they will *not* receive medications or counseling.

The modified Zelen design is a novel feature of this trial, which will permit a true population-based study in which all smokers, regardless of their level of motivation, will be included in the study. By consenting patients after random assignment and treatment, the study does run the risk of dilution bias introduced by participants refusing consent post randomization [22]. A recent comprehensive review of Zelen trials found that most trials experience low dilution bias (single-digit percentages of refusal to consent or crossover). This suggests that the potential for recruiting a more representative and generalizable sample greatly outweighs the dilution bias introduced at the time of consent.

The Bayesian adaptive design approach is another novel feature of this trial. It is a highly efficient and ethical strategy for comparative effectiveness clinical trial design because it allocates more patients to effective treatments and can answer the research question earlier than conventional designs [57, 58]. In this approach one primary endpoint is used to drive the adaptive randomization. This endpoint is compared across study groups periodically, and more patients are randomized to the stronger arm until a predetermined probability that one arm has “maximum utility” is reached, which signals the end of the comparative trial.

This trial will identify the impact of default tobacco-cessation treatment, for an entire population of smokers, on (1) use of medications and counseling and (2) cessation. It will identify the costs and cost-effectiveness of changing the default, and examine psychological mediators of change based on decision theory. This contribution is significant because it will definitively determine the impact of routinely assessing smokers’ readiness to quit in real-world clinical practice. Assessing readiness is an integral step in the “5 As” of tobacco-cessation treatment (*Ask, Advise, Assess* [*readiness to quit*]*, Assist, Arrange*) [3]. But the *Assess* step is only supported by “C-level” evidence of effectiveness, as there are no trials that establish that it has a positive impact on cessation [3]. Indeed, we hypothesize that the *Assess* step may actually reduce the number of smokers that receive evidence-based treatment. If our hypothesis is confirmed, it could transform the “5 A” approach and increase access to treatment for the more than 30 million smokers that visit a health care provider each year [59, 60].

## Trial status

Recruitment of participants started on 12 September 2016 and at the time of submission of this manuscript, enrollment is ongoing (Additional file 1).

## Abbreviations

CFI: Comparative Fit Index
DSM: Data Safety and Monitoring
DSMB: Data and Safety Monitoring Board
EHR: Electronic health record
EQUIP: Enhancing Quitline Utilization among In-Patients
ICER: Incremental cost-effectiveness ratio
IRB: Institution Review Board
ITT: Intent-to-treat
KUMC: University of Kansas Medical Center
MAR: Missing at random
MNAR: Missing not at random
NIH: National Institutes of Health
NRT: Nicotine Replacement Therapy
PI: Principal investigator
QALYs: Quality-adjusted life years
RCT: Randomized controlled trial
RMSEA: Root Mean Square Error of Approximation
SAS: Statistical Analysis System
SPSS: Statistical Package for the Social Sciences
STEMI: ST-elevation myocardial infarction
UKanQuit: University of Kansas Hospital Smoking Cessation Service
